## Abstract

**Background:**

Parkinson’s disease (PD) is a chronic progressive disorder leading to increasing disability. While the symptoms and needs of patients in the early stages of their disease are well characterized, little information is available on patients in the late stage of the disease.

**Methods/design:**

The Care of Late-Stage Parkinsonism (CLaSP) study is a longitudinal, multicenter, prospective cohort study to assess the needs and provision of care for patients with late stage Parkinsonism and their carers in six European countries (UK, France, Germany, Netherlands, Portugal, Sweden). In addition, it will compare the effectiveness of different health and social care systems. Patients with Parkinsonism with Hoehn and Yahr stage ≥IV in the “On”-state or Schwab and England stage 50% or less are evaluated at baseline and three follow-up time-points. Standardised questionnaires and tests are applied for detailed clinical, neuropsychological, behavioural and health-economic assessments. A qualitative study explores the health care needs and experiences of patients and carers, and an interventional sub-study evaluates the impact of specialist recommendations on their outcomes.

**Discussion:**

Through the combined assessment of a range of quantitative measures and qualitative assessments of patients with late stage parkinsonism, this study will provide for the first time comprehensive and in-depth information on the clinical presentation, needs and health care provision in this population in Europe, and lay the foundation for improved outcomes in these patients.

**Trial registration:**

The protocol was registered at ClinicalTrials.gov as NCT02333175 on 07/01/2015.

## Introduction

Parkinson’s disease (PD) is the second most common neurodegenerative disorder, affecting approximately 1.2 million people in Europe [1]. There is increasing disability with disease progression, but whilst there is an abundant number of studies on the health and social care needs of patients in the early stages of PD, there is surprisingly little information on the medical and care needs of the late stage population, and how these needs are currently met. In addition, there is little information on the use and effectiveness of the pharmacological and non-pharmacological interventions for PD in these late stages, when there may be multiple features and comorbidities. These include motor complications and non-motor symptoms such as behavioral and psychological symptoms, autonomic disturbances and sleep disorders, which can contribute to the burden of the disease to patients and their carers [2, 3] and may lead to nursing home placement and higher mortality [3–5]. Most studies on the management and care needs of patients with PD include only small subgroups in the late stages of the disease [6, 7] and patients in Hoehn and Yahr stages IV and V [8] are usually excluded from clinical trials [9]. In specialist practice, the proportion of patients in the late stages is also underrepresented as they are often too disabled to attend hospital or office-based appointments and do not receive adequate care [10]. It is therefore currently relatively unknown what the exact health care needs are in patients with late stage Parkinsonism, and no large study has evaluated the provision of health care for these patients and associated costs across different European health care systems. Small studies point to an increased use of health as well as social care resources (hospitalization and institutionalization) in late PD stages [11–14] and a high need for informal care with increased caregiver burden [12, 14].

The Care of Late-Stage Parkinsonism (CLaSP) study aims to establish a large European cohort of patients with parkinsonism in the late stage of the disease (i.e. HY stages I*V*/V in the “On”-stage or Schwab and England stage 50% or less) in six European countries to examine the health and social care needs of this patient group and their carers, available health care provision and costs to society. Alongside the cohort study, eligible patients are randomised in an interventional trial evaluating the impact of specialist recommendations in patients in late stages of Parkinsonism, and a qualitative study explores the health care needs and experiences of patients and carers. This article describes in detail the methodology of the study and the assessments used in this large and unique cohort. An abstract on the study design has been previously published [15].

## Methods

### Study design

The CLaSP study is a longitudinal multicenter cohort study of patients with late stage Parkinsonism and their carers. In the six European health care systems (London and Luton, UK; Marburg-Giessen, Essen, and Munich, Germany; Nijmegen, The Netherlands; Bordeaux, France; Lisbon, Portugal; and Lund, Sweden) patients with late-stage Parkinsonism and their informal carers are identified from neurology, care of the elderly, palliative care, and primary care settings. Patients for the qualitative interviews and for the intervention trial are recruited from the participants in the cohort study.

### Cohort study

#### Inclusion criteria

Patients are eligible for enrolment in the CLaSP study, if they had been diagnosed for at least seven years with Parkinsonism and are classified as Hoehn and Yahr stage (HY) IV or V in the “On”-state OR have developed significant disability (Schwab and England stage ≤50%) in the “On”-state [16]. Established clinical criteria (UK Parkinson's Disease Society Brain Bank Diagnostic Criteria [17]) are applied to distinguish subjects with PD from those with different atypical parkinsonian syndromes. However, since distinction in late stages of the disease can be difficult and patient needs are likely to be similar despite different underlying pathology, patients with atypical parkinsonian disorders are not excluded.

#### Exclusion criteria

Patients with PD in HY stages I-III are excluded as well as patients with a diagnosis of “symptomatic PD” such as normal pressure hydrocephalus or drug-induced Parkinsonism, except if persisting following discontinuation of the causative drug.

Assessments (see Table 1) are conducted in person at baseline and at 12 months, with optional telephone follow-up at 6 and 18 months.

**Table 1 Tab1:** Assessment instruments and time points of application

Scales/Domains	Instruments	Reference	Application at			
			T1	T2	T3	T4
Patient-completed						
Quality of life and health status	EuroQol instrument	[20]	x	x	(x)	(x)
	PDQ-8^a^	[21]	x	x	x	x
Meaning in Life	SMiLE	[22]	x	x	(x)	(x)
Satisfaction with Care	Likert scale		x	x	(x)	(x)
Carer-completed						
Quality of life and health status	EuroQol instrument	[20]	x	x	(x)	(x)
Patient Quality of Life	DEMQOL-Proxy^b^	[23]	x	x	x	x
Satisfaction with Support	Likert Scale		x	x	(x)	(x)
Caregiver burden	Zarit burden scale	[24]	x	x	(x)	(x)
Clinician-completed						
Activities of daily living	UPDRS (pt. II)	[25]	x	x	x	x
	Schwab&England	[16]	x	x	x	x
Demographic/social data			x			
Checklist of symptoms, treatments, tests						
Comorbidities	Charlson-Index	[34]	x	x	(x)	(x)
Resource Utilisation questionnaire		[19]	x	x	x	
Clinical rating/judgement	CGI	[26]	x	x	x	x
	Hoehn and Yahr	[8]	x	x	(x)	(x)
	UPDRS (pts. I, III, IV)	[25]	x	x	(x)	(x)
Cognitive assessment	MMSE+clock drawing+fluency	[27–29]	x	x	(x)	(x)
	Pill questionnaire	[18]	x	x	(x)	(x)
Neuropsychiatric and other non-motor symptoms	Neuropsychiatric Inventory (NPI-12)	[30]	x	x	(x)	(x)
	Non-motor symptom scale	[31]	x	x	x	x
	Geriatric Depression Scale (GDS)	[32]	x	x	(x)	(x)
Basic palliative assessment	ESAS-(PD)	[33]	x	x	(x)	(x)
Supine and standing blood pressure			x			
Evaluation of Implementation				x		

^a^in patients with a diagnosis Parkinson’s disease only; ^b^in patients with dementia instead of PDQ8 and EQ-5D; (×) optional; T1 = Baseline with randomisation, T2: 6 months after baseline (in-person for intervention participants only), T3: 12 months after baseline (telephone with patient and/or carer or optional in-person assessment), and T4: 18 months after baseline (telephone with patient and/or carer or optional in-person assessment). Abbreviations used: *PDQ-8* The Parkinson’s Disease Questionnaire, short form, *SMiLE* Schedule for Meaning in Life Evaluation. Euroqol-Instrument (EQ-5D Index and visual analogue scale), *DEMQOL-Proxy* health-related quality of life for people with dementia - proxy version. *CGI* Clinical Global Impression, *UPDRS* Unified Parkinson’s Disease Rating Scale, *UPDRS* Unified Parkinson’s Disease Rating Scale, *MMSE* Mini Mental State Examination, *ESAS-PD* Edmonton Symptom Assessment System – Parkinson’s Disease

### Interventional trial

#### Inclusion criteria

For the interventional trial, patients are eligible if they experience at least one of the following insufficiently treated symptoms/problems (based on clinical judgment): motor parkinsonism according to Unified Parkinson’s Disease Rating Scale (UPDRS; including nocturnal motor problems), levodopa-induced motor complications, including Off-time > 50% of waking day (assessed on UPDRS part IV), moderately disabling dyskinesias (item 33 ≥ 2) or Off time dystonia, PD dementia (defined according to MDS Task Force definition [18], depression (GDS > 4 points) not receiving adequate treatment, psychotic symptoms, agitation/ aggression; anxiety and irritability/ liability (all NPI items > 4 points), symptomatic orthostatic hypotension, pain, constipation, urinary symptoms, insomnia or daytime sleepiness, falls OR are treated medications potentially associated with exacerbation of PD-related problems: (a) typical antipsychotics other than quetiapine or clozapine, anticholinergics, benzodiazepines, pills with protein rich meal, antihypertensives in symptomatic hypotensive patients, valproate, calcium antagonists, other medications with side effect exacerbating PD motor or non-motor symptoms OR are at risk of contractures and skin ulceration OR inadequate management of dysphagia with risk of choking, of dysarthria or of hypersalivation OR live in an inadequate home environment.

#### Exclusion criteria

Patients with parkinsonism seen by a movement disorders specialist in the four months prior to inclusion, and patients unable to comply with management plans (such as attending physiotherapy or change of medication) are excluded from the intervention trial.

Participants fulfilling the inclusion criteria are randomised in an open-label trial to two-arms in 3:1 allocation: to an intervention or care as usual, and assessed at 6 months (in-person; primary outcome) and optionally at 12 and 18 months (telephone review, secondary outcome). The intervention consists of individually tailored treatment strategies suggested by specialists after review of the baseline assessment and treatment regime.

### Qualitative study

#### Inclusion criteria

For the qualitative study, approximately 10 PD patients and an informal carer in each participating center (London, UK, Lund, Sweden, and Lisbon, Portugal) are being recruited consecutively. For inclusion, the same criteria apply as for the cohort study.

#### Exclusion criteria

In addition to the exclusion criteria of the cohort study, patients unable to communicate in words (because of either dysarthria or language problems) are excluded from the qualitative study.

Semi-structured interviews with patients and informal carers are conducted on the needs of patients with late stage Parkinsonism. The questions addressed are: perceived met and unmet needs, including palliative care needs, the experience and perceived impact of receipt of services, formal and informal support, exploration of deficits and barriers to adequate care provision, identification of factors influencing the decision as to whether patients are cared for at home or in residential care/institution, and advanced care planning (attitudes of patients towards advance directives and preferred place of death). These interviews are audio-recorded and transcribed; and then subject to thematic analysis aided by the N-VIVO computer program to identify the range of experiences and perceived needs and outcomes of different services provisions and treatments.

### Recruitment strategies

The major challenge in the CLaSP project is the identification, recruitment, and assessment of patients in late stages. We particularly aim to include patients who are not under regular specialist follow-up. Therefore, several methods to reach this target group are employed, particularly aiming to recruit individuals not currently attending routine specialist clinics: The centers contacted general practitioners, hospitals, nursing homes, patient advocate groups as well as self-help groups to draw attention to the CLaSP project and identify and recruit eligible patients.

### Clinical assessment

#### Cohort study

The assessment of patients and carer comprise of standardised questionnaires to evaluate disease severity, comorbidities, depression, cognition, non-motor symptoms, quality of life in patients and carers as well as caregiver burden (for an overview of timepoints and instruments/ questionnaires applied, see Table 1). The patients of the cohort study are followed up in person at 12 months and optionally via telephone at 6-month and 18 months. A special resource use questionnaire for patients with Parkinson’s disease and their carers was developed and used in a previous health economic cost of illness study [19] was applied. The questionnaire was adapted to the requirements of the respective country-specific health care system.

#### Intervention study

Baseline assessments are repeated at 6 months (T2) in person and on the telephone at 12 months. In addition, at T2, information is collected whether the individual intervention has been implemented into the patient’s treatment schedule.

### Outcome measures

The following instruments are used to collect data on the patients and their caregivers at different time points during the study (see also Table 1):

Health-related quality of life in PD patients and their caregivers is evaluated using the self-completed, generic EuroQol instrument, which comprises a questionnaire (EQ-5D) and a visual analogue scale (EQ VAS) [20]. The questionnaire consists of five questions with three levels of possible answers, representing the dimensions Mobility, Self-Care, Usual Activities, Pain/Discomfort, and Anxiety/Depression. In the EQ VAS, the participants rate their subjective health status on a scale with a range of 0 to 100 with higher scores indicating a better quality of life. Additionally, the self-administered, disease-specific PDQ-8 instrument is used in patients [21]. It is derived from the PDQ-39 and assesses eight domains: Activities of Daily Living, Attention and Working Memory, Communication, Depression, Quality of Life, and Social Relationships. Higher scores in the PDQ-8 indicate more problems and a worse quality of life. Satisfaction with Care is assessed in the patient via a 5-point Likert scale, with higher rating reflecting less satisfaction. The Schedule for Meaning in Life Evaluation (SMiLE) is an instrument to assess individual meaning in life [22]. First, the patients list one to seven areas that provide meaning to their lives and subsequently rate the current level of importance and satisfaction of each area. From these answers, a sum score can be calculated where higher scores indicate higher satisfaction in life. The DEMQOL proxy is used to obtain caregiver reports on the patient’s quality of life [23]. In our study, it is applied in patients with dementia instead of the PDQ-8 and the Euroqol instrument. Satisfaction with Support is assessed in the caregiver via a 5-point Likert scale, with higher rating indicating less satisfaction. The caregiver burden is assessed via the revised 22-items version of the Zarit Burden Scale [24]. Each item on the interview is answered by the caregiver on a 5-point scale with higher sum scores reflecting higher burden on the caregiver. The clinician completes the following assessments on the patient: For the clinical evaluation of Parkinson’s disease, the Unified Parkinson’s disease Rating Scale (UPDRS) is used to assess patients in four sections: Mentation, Behavior and Mood, Activities of Daily Living, Motor Examination, and Complications of Therapy [25]. In addition, the Hoehn and Yahr scale (HY) is used to describe the stage of PD severity [8]. The patient’s ability to perform activities of daily living is assessed with the Schwab & England Scale [16]. The score reflects the patient’s situation on a 0 (= complete dependence/bedridden) to 100% (= complete independence) scale. The Clinical Global Impression (CGI) rating scale is used to evaluate the patients’ symptom severity and change of symptoms over time [26]. The Mini-Mental State Examination (MMSE) is an assessment tool for general cognitive impairment, with higher overall total scores (range 0–30) indicating better performance [27]. The clock-drawing test is used for screening for cognitive impairment and dementia [28], which is sensitive to visuo-spatial impairment. The verbal fluency test (letter s) is used as a short test of executive function [29]. The Pill Questionnaire is a screening tool for mild cognitive impairment in nondemented Parkinson’s disease patients, using the ability to remember Parkinson’s disease-specific medications as an indicator of cognitive function [18]. The Neuropsychiatric Inventory (NPI-12) is an informant-based instrument to assess the presence and severity of twelve neuropsychiatric symptoms (i.e. delusions, hallucinations, agitation/aggression, dysphoria/depression, anxiety, euphoria/elation, apathy/indifference, disinhibition, irritability/lability, aberrant motor behaviors, night-time behavioral disturbances, appetite/eating disturbances) in patients with dementia, as well as informant distress [30]. To assess the occurrence and severity of non-motor symptoms, the Non-Motor Symptom Scale (NMSS) is used [31]. The Geriatric Depression Scale (GDS) is a 15-item screening tool with higher overall total scores (range 0–15) indicating higher depression levels [32]. The modified Edmonton Symptom Assessment System Scale for PD (ESAS-PD) was modified from symptom assessment in palliative care for patients with PD [33]. Comorbidities are assessed with the Charlson Comorbidity Index (CCI) [34].

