#### Secondary endpoints

Secondary endpoints are the patients’ quality of life, mental health, disease severity and disability, non-motor symptoms scale score, occurrence of disease severity milestones (psychosis, dementia, falls, wheelchair-bound, institutionalization, and death), satisfaction with care as well as caregiver burden.

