### Statistical analysis

Categorical variables will be analysed by absolute and relative frequency, continuous variables by median, mean, standard deviation, 95% confidence interval, minimum, and maximum. Differences in continuous variables between groups (e.g. countries) at time points will be tested by analysis of variance (ANOVA) and analysis of covariance (ANCOVA) or their nonparametric analogues, respectively. Differences between groups at time points assessed by proportions will be analysed by the Chi-square or Fisher’s exact test, if applicable, and logistic regression.

Changes in continuous variables between two time points will be evaluated by the paired t-test or Wilcoxon signed rank test, respectively. Changes in proportions between two time points will be analysed by the McNemar test. Longitudinal analyses will be performed by applying linear and generalized linear mixed models with patient or carer as random effect, main effects for country and time, as well as a country-by-time interaction term and possible confounders.

In the intervention study, all analyses of outcome parameters will be done in the intent-to-treat population. The primary efficacy analysis will be to investigate the treatment effect on absolute change in UPDRS-ADL score from baseline to month 6 in the intervention and standard care group. Data will be analyzed using ANCOVA with categorical factors (treatment, country, dementia, residence) and baseline UPDRS-ADL score as a covariate. The null hypothesis “no difference in the primary endpoint between the intervention group and standard care group” will be tested against the alternative hypothesis “difference in the primary endpoint between both groups”. The primary efficacy analysis will be repeated using the per-protocol population to confirm the overall study results. Safety data will be analyzed in the as-treated population.

All tests will be performed two-sided, *p* values < 0.05 will be considered statistically significant.

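### No quality-of-life scale spans all participants, and patients with atypical parkinsonism without dementia have no required scale at 12 months

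*Protocol article*

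**What the plan says.** All references are to the protocol article.

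- **Dementia.** Outcome measures says of DEMQOL-Proxy that "it is applied in patients with dementia instead of the PDQ-8 and the Euroqol instrument". Footnote b of Table 1 repeats the substitution: "in patients with dementia instead of PDQ8 and EQ-5D".
- **Diagnosis.** Footnote a restricts PDQ-8: "in patients with a diagnosis Parkinson’s disease only". The cohort's Inclusion criteria nevertheless state that "patients with atypical parkinsonian disorders are not excluded".
- **Visit marks in Table 1.** The patient EuroQol row is "EuroQol instrument [20] x x (x) (x" (its last bracket closes after the quotation): required at T1 and T2, optional at T3 and T4. PDQ-8 is required at all four visits, and so is DEMQOL-Proxy: "DEMQOL-Proxy^b^ [23] x x x x".
- **Endpoints.** The patients' quality of life is listed under Secondary endpoints with no scale named. Incident dementia is expected, since the same list includes "occurrence of disease severity milestones (psychosis, dementia, falls, wheelchair-bound, institutionalization, and death".
- **Analysis.** For the intervention study, Statistical analysis says that "all analyses of outcome parameters will be done in the intent-to-treat population". Dementia is a randomisation stratum (Sample size) and a factor in the primary ANCOVA.
- **The 12-month visit.** Primary endpoint makes month 12 the cohort's primary time point, and Clinical assessment makes it the cohort's in-person follow-up.

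**The concern.** EuroQol is the one patient scale in the schedule that could serve every diagnosis. It is withdrawn in dementia and becomes optional at the visit that matters most to the cohort. Patients with and without dementia are then measured on different instruments, by different raters, with no common measure to link them. A mixed model or ANCOVA cannot bridge that, and an analysis plan cannot recover values that the schedule did not require. One group of eligible patients may have no quality-of-life value at 12 months at all, depending on what each site chooses to do. Comparing countries is a main aim, so site-dependent completion is a direct threat to that comparison.

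**Working it through.** **Step 1. Apply the rules to each patient group.** Required patient quality-of-life scales, from Table 1, its footnotes and Outcome measures:

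| Group | T1 | T2 (6 months) | T3 (12 months) | T4 (18 months) |
|---|---|---|---|---|
| PD, no dementia | PDQ-8, EuroQol | PDQ-8, EuroQol | PDQ-8 | PDQ-8 |
| Atypical, no dementia | EuroQol | EuroQol | none | none |
| Dementia, any diagnosis | DEMQOL-Proxy | DEMQOL-Proxy | DEMQOL-Proxy | DEMQOL-Proxy |

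No scale appears in all three rows at any visit. The empty cells are confined to T3 and T4. For patients in the cohort only, the 6-month contact is itself optional, so after baseline the atypical group without dementia has no required measure at any required contact.

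**Step 2. Compare the statements about 12 months.**

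- The text above Table 1, and Clinical assessment (Cohort study): the cohort is seen in person.
- Clinical assessment (Intervention study): the baseline assessments are repeated by telephone, which would include EuroQol.
- Interventional trial, Exclusion criteria: 12 months is an optional telephone review.
- Table 1 footnote: telephone, or an optional in-person assessment, with EuroQol marked (x).

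These do not agree. If the second governs, EuroQol is due at 12 months for trial patients, but that statement does not reach cohort-only patients.

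**Step 3. Size of the gap.** The plan has no figure of its own on this point and gives no rates. Assume a share d with dementia of 20–50% and a share a with atypical disease of 5–20%, independent of each other.

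- No required scale at T3 = (1 − d) × a. Lowest: 0.50 × 0.05 = 2.5%. Highest: 0.80 × 0.20 = 16%. Of 6 × 70 = 420 cohort patients: 10.5 to 67.2.
- Covered by PDQ-8 = (1 − d)(1 − a): 0.50 × 0.80 = 40% to 0.80 × 0.95 = 76%.
- Covered by EuroQol, at most 1 − d: 50% to 80%.
- Covered by DEMQOL-Proxy = d: 20% to 50%.

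**Step 4. What this means for the 6-month trial comparison.** The plan's sample size reproduces. With 4.8/10 = 0.48 SD and 3:1 allocation, the control group needs (1 + 1/3)(1.96 + 0.842)²/0.48² = 45.4, so 46, with 138 in the intervention group. Dividing by 0.8 × 0.8 gives 71.9 and 215.6, hence 72 and 216. Borrow the same 0.48 SD for EuroQol purely as a yardstick. Power = Φ(0.48/√(1/n₀ + 1/n₁) − 1.96):

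- all 46 + 138: 80%;
- EuroQol subset at d = 20% (36.8 + 110.4): 71%;
- EuroQol subset at d = 50% (23 + 69): 51%.

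**Step 5. Incident dementia, if the instrument follows current status.** With a share i of the rest developing dementia by T3, self-rated change remains possible for (1 − d)(1 − i), DEMQOL-Proxy change for d, and neither for (1 − d) × i:

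- d = 20%, i = 5%: 76%, 20%, 4%;
- d = 30%, i = 10%: 63%, 30%, 7%;
- d = 50%, i = 15%: 42.5%, 50%, 7.5%.

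These are upper limits for self-rated change, before deaths and before skipped optional EuroQol.

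**The case against.** A dementia-specific proxy scale is a deliberate choice where self-report may be unreliable, and a proxy EuroQol would exchange one comparability problem for another. That stands, which is why the proxy EuroQol is offered only as an addition. It does not explain why EuroQol is optional at 12 months for patients who can complete it.

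A reader might infer more than the documents support:

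- *Change is available only in patients who stay cognitively intact.* Not so. DEMQOL-Proxy is required at all four visits, so patients with dementia at baseline have a change score. It simply cannot be pooled with the self-rated scales. A general underestimate of decline is not shown.
- *The health-economic comparison leaves out patients with dementia.* Not so. The resource-use questionnaire is required at T1 to T3 without a dementia restriction, and Statistical analysis specifies no cost-utility analysis. The reference to cost-effective care in the Discussion is an aspiration.
- *Atypical patients have no measure at all.* Not so. EuroQol is required at T1 and T2.
- *Patients who develop dementia certainly lose their change score.* This is an inference. The article states no rule for switching instruments, dementia status at baseline is already used for stratification, and the full protocol or analysis plan may settle it.

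Finally, the rates in the working are all assumed, and the order of the secondary endpoints implies no hierarchy.

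**Conclusion.** The point holds in a limited form. No patient quality-of-life scale covers all participants at any visit, so this endpoint cannot be analysed on one scale in the intent-to-treat population. Patients with atypical parkinsonism and no dementia have no required scale at 12 months as Table 1 stands. The descriptions of that visit contradict one another, so the article does not settle whether EuroQol is due then.

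Under the assumed rates, the 12-month gap affects 2.5–16% of patients and no single scale reaches more than about 80%. A further 4–7.5% could lose their change score, but only if the instrument follows current dementia status. The 6-month comparison has a required scale in every group, though not a common one. The primary UPDRS-ADL endpoint is required of all patients at every visit and is not affected.

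**What to change.** 1. In Table 1, change patient EuroQol at T3 from (x) to x. Reconcile this with the Intervention study paragraph under Clinical assessment and with the differing descriptions of the 12-month contact. T4 can stay as it is: the 18-month contact is itself optional, so a required mark there would not secure the data.
2. State that the instrument set assigned at T1 is kept for the change analysis, and that DEMQOL-Proxy is added, not substituted, if dementia develops later.
3. Optionally, have the carer complete a proxy EuroQol for the patient wherever DEMQOL-Proxy is given, with proxy status recorded and carried in the analysis. This would give one generic scale across the dementia strata.

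The cost is an amendment to Table 1 and its footnotes, and five questions plus a visual scale for the patient, or for a carer who already completes questionnaires. The drawbacks are that proxy and self-ratings are not fully interchangeable, and that self-report after dementia develops may be missing or hard to interpret.
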